### ***1.8 Study pathology***

COVID-19.

### ***1.9 Data from the medicinal product***

Not applicable.

### ***1.10 Type of population and number subjects***

Study population will be subjects who underwent SARS-Cov-2 antigen test within the Cruïlla festival or the CanetRock Festival, and who are registered at the Catalan Public Health System. Overall, 40000 people underwent SARS-Cov-2 antigen test within the Cruïlla festival. For the CanetRock Festival, 22000 people underwent SARS-CoV-2 antigen test before attending the festival. The study will also include data from a control cohort, made of subjects that did not attend the event but were paired with the attendees. Pairing will be made 1:1 based on age, gender, geographical area and Covid-19 immune status (vaccine/previous infection).

### ***1.11 Calendar***

|                               |               |
|-------------------------------|---------------|
| Ethics Committee application: | October 2021  |
| Data management:              | November 2021 |
| Data analysis:                | November 2021 |
| Final report:                 | November 2021 |

### ***1.12 Financing source***

Internal research funding sources within both partners, FLS and Health Ministry of *Generalitat de Catalunya*.

### 3 RATIONALE

The importance of the live events industry to the economy is significant. However, the public health response to COVID-19 led to an unprecedented closure in the entertainment industry. Although substantial advances have been made to re-open other industries, there has been limited experience on the reopening of live events such as live music concerts, festivals, or congresses. Because these experiences require people to be very close together, live events generally create conditions that favour virus transmission. Thus, preventive measures need to be adopted. However, there are no clear policy protocols to permit the return of live entertainment at full capacity.

Several self-care and risk mitigation strategies are currently being used.

On the one hand, facemasks wearing, handwashing, and capacity reduction to promote social distancing are non-pharmaceutical interventions available to reduce the basic reproduction rate of the virus.

Infection or immunity passports, which refer to tests that demonstrate negative infection status or immunity have also been used to re-open activities such as travelling.

Finally, given the continued roll out of vaccinations, vaccine passports have become a new criterion to demonstrate immunity in certain activities.

How to combine all these strategies in a cost-efficient manner to celebrate safely live events is still under debate.

On July 3, 2021, CanetRock music festival took place in Canet, a town located 40 km north-east of Barcelona, Catalonia, Spain. On July 8, 9 and 10, 2021, Cruïlla music festival took place in Barcelona, Catalonia, Spain. To reduce the risk of SARS-CoV-2 transmission within the festival, the organizers applied the following measures.

- Attendees to the festival were screened for SARS-CoV-2 infection with Antigen Rapid Diagnostic Test (Ag-RDT) via a nasopharyngeal swab.
- Non-contact body temperature screening was performed.
- Attendees were given a certified Filtering facepiece 2 (FFP2) mask. The use of the mask was compulsory whenever people were not eating/drinking.

This study aims to compare the prevalence of COVID-19 among those attending the Cruïlla festival and a control cohort, before and after attending the festival. Independently, it will also compare the prevalence of COVID-19 among those attending the CanetRock festival and its corresponding control cohort, before and after attending the festival. We will also characterize the subjects developing or not COVID-19 within 14 days after attending the festival. This characterization will be specially focused on the socio-demographic characteristics of the attendees (age, gender, geographic location), the individual level of COVID-19 immunity (based on vaccination and/or previous infections) and the behaviour at the festival (number of days attended, and days of attendance).

Catalan Health Department (*Conselleria de Salut, Generalitat de Catalunya*) has sponsored this study in collaboration with [name] from the *Hospital Germans Trias i Pujol* and the *Fundació Lluita contra la Sida*, the Cruïlla Barcelona Festival and the CanetRock Festival. This analysis will provide information regarding the

effectiveness of preventive measures against COVID-19 transmission taken during the festivals, which will be beneficial for the organization of future events.

## **4 OBJECTIVES**

### **4.1 *Primary objective***

Prevalence of Covid-19 among those attending the Cruïlla Music festival 2021 and the CanetRock music festival 2021.

### **4.2 *Secondary objective***

Characterization of subjects according to development or not of COVID-19 within 14 days after attending the festival.

## **5 INFORMATION SOURCE AND FIELD**

Information source will be data captured by Cruïlla festival and CanetRock festival and by the Catalan Health Department using standard procedures for their activities (see section 7.1 Data Protection for details).

## **6 STUDY DESIGN**

### ***6.1 Definition of study population: Selection criteria***

Study population will be subjects who underwent SARS-Cov-2 antigen test within the Cruïlla festival, and a control cohort of paired subjects according to the following characteristics of the attendees (age, gender, geographical area, Covid-19 immune status (vaccine/previous infection). In parallel, a second study population will comprise subjects who underwent SARS-Cov-2 antigen test within the CanetRock festival, and a control cohort of paired subjects according to the previously specified criterion.

### ***6.2 Observation period***

Data regarding the number of SARS-CoV-2 positive test results in each cohort will be collected considering 14 days before and 14 days after the festival (24th June - 24th July).

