### ***6.3 Treatment and exposure description***

For the Cruïlla Festival cohort, subjects with negative results at the SARS-Cov-2 Ag-RDT screening were exposed to the Cruïlla festival for 1, 2 or 3 days.

For the CanetRock Festival cohort, subjects with negative results at the SARS-Cov-2 Ag-RDT screening were exposed to the CanetRock festival for 1 day.

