## **7 VARIABLES AND MEASURE INSTRUMENTS. MEASUREMENTS DEFINITION AND DESCRIPTION**

### **7.1 Primary endpoint**

To study the prevalence of Covid-19 among those attending the festivals, the following endpoint will be analysed:

- Frequency of subjects attending to the Cruïlla festival who report a positive test on SARS-CoV-2 within the 14 days after the festival.
- Frequency of subjects attending to the CanetRock festival who report a positive test on SARS-CoV-2 within the 14 days after the festival.
- Frequency of subjects in each control cohort who report a positive test on SARS-CoV-2 within the 14 days after the festival.

Additional analysis will be performed excluding the following subjects, who will be considered as not infected during the festivals:

- Subjects who tested positive on SARS-CoV-2 6 days after their last day attending the festival.
- Subjects who tested positive within 2 days after attending the festival.

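### The single window in section 6.2 (24 June to 24 July) fits only Cruïlla; for CanetRock it cuts the pre-festival period from 14 days to 9, so the planned before/after comparison cannot be done as stated

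*Protocol*

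**What the plan says.** Protocol section 6.2 (Observation period) combines a rule and a pair of dates in one sentence: "considering 14 days before and 14 days after the festival (24th June - 24th July"). The sentence covers all cohorts: "Data regarding the number of SARS-CoV-2 positive test results in each cohort will be collected". No other section gives a separate window for CanetRock.

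Section 3 (Rationale) dates the two festivals differently: "On July 3, 2021, CanetRock music festival took place in Canet", and "On July 8, 9 and 10, 2021, Cruïlla music festival took place in Barcelona". Section 6.3 confirms that CanetRock attendees "were exposed to the CanetRock festival for 1 day".

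Two uses of the data depend on the window:

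- The primary endpoint in section 7.1 looks forward only. For CanetRock it is "Frequency of subjects attending to the CanetRock festival who report a positive test on SARS-CoV-2 within the 14 days after the festival".
- Section 3 also sets out a comparison between "those attending the CanetRock festival and its corresponding control cohort, before and after attending the festival". The design summary in section 1.7 likewise plans to compare positives in each cohort before and after the festival.

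**The concern.** The two festivals were held five to seven days apart, so a rule of 14 days either side cannot give the same calendar dates for both. The dates printed in section 6.2 therefore have to be wrong for at least one of them, and CanetRock is not a minor part of the study. Sections 1.10 and 6.5 give 22,000 people tested there against 40,000 at Cruïlla, which is 22,000/62,000 = 35% of those tested.

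At stake is the before/after comparison for CanetRock. If the registry extraction follows the printed dates, part of the pre-festival period is never drawn, and no later analysis step can restore it. The before and after periods would then differ in length, so the raw counts would rise from before to after even if nothing had happened at the festival.

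**Working it through.** **Inputs**

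- Rule: 14 days before and 14 days after (section 6.2).
- Printed dates: 24 June to 24 July (section 6.2).
- Cruïlla: 8, 9 and 10 July 2021 (section 3).
- CanetRock: 3 July 2021, one day (sections 3 and 6.3).

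**Formula.** Window start = first festival day − 14 days. Window end = last festival day + 14 days.

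**Step 1: reproduce the plan's own figure.** For Cruïlla, 8 July − 14 days = 24 June and 10 July + 14 days = 24 July. This is exactly the printed window.

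**Step 2: apply the same rule to CanetRock.** 3 July − 14 days = 19 June and 3 July + 14 days = 17 July. This is not the printed window.

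**Step 3: compare the printed dates with each festival.**

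| | Cruïlla | CanetRock |
|---|---|---|
| Window under the rule | 24 June to 24 July | 19 June to 17 July |
| Days before, printed dates | 14 (24 June to 7 July) | 9 (24 June to 2 July) |
| Festival days | 3 | 1 |
| Days after, printed dates | 14 (11 to 24 July) | 21 (4 to 24 July) |
| Total days | 31 | 31 |

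For CanetRock the printed dates omit 19 to 23 June, which is 5 of 14 days (36%), and include 18 to 24 July, which is 7 days more than the rule allows.

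**Step 4: effect on a raw before/after ratio within one cohort.** Assume flat daily incidence and no festival effect. The expected count is then proportional to the number of days, so the after/before ratio is (days after)/(days before).

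- Rule followed: 14/14 = 1.00.
- Printed start date, counting stopped at 14 days after: 14/9 = 1.56.
- Printed start and end dates both used for counting: 21/9 = 2.33.

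**Step 5: dependence on the flat-incidence assumption.** The protocol gives no incidence figures, so a range has to be assumed. If daily incidence changes by a constant factor 1 + g, the last 9 of the 14 pre-festival days hold the share [1 − (1+g)^−9]/[1 − (1+g)^−14] of the 14-day count.

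- g = 0: 9/14 = 64%.
- g = +10% per day: (1 − 0.424)/(1 − 0.263) = 0.576/0.737 = 78%.
- g = −5% per day: 0.95^5 × (1 − 0.95^9)/(1 − 0.95^14) = 0.774 × 0.370/0.512 = 56%.

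Over this assumed range the truncated period holds 56% to 78% of the intended pre-festival count.

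**The case against.** The strongest reply is that the primary analysis is untouched, and most of that reply stands.

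- The CanetRock endpoint in section 7.1 ends on 17 July, inside the printed window. Every day it needs is collected, and counting to 24 July would mean ignoring section 7.1 as well as the 14-day rule in section 6.2 itself. A reader might infer that the CanetRock primary result is wrong as planned; the document does not support that. The 2.33 is therefore an outer case.
- The same window applies to attendees and their controls, so unequal before and after lengths do not by themselves bias that contrast. If both groups follow the same daily course, the factor 14/9 appears in each and cancels when their after/before ratios are compared. It distorts only the change within a cohort.
- None of the endpoints in section 7.1 uses a pre-festival count. The before/after comparison comes from sections 1.7 and 3.

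A reader might also infer that a comparison of CanetRock with Cruïlla would be distorted. No such comparison is planned: sections 3 and 8.1 treat the festivals independently, each with its own population.

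One part of the defence fails. The printed dates could be read as a common extraction period, with the 14-day rule applied afterwards for each festival. A period covering both festivals would have to begin on 19 June, and this one begins on 24 June. The five pre-festival days are missing on that reading too.

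**Conclusion.** The point holds. For CanetRock, the rule and the dates in section 6.2 contradict each other. If extraction follows the dates, the 14-day pre-festival count for CanetRock attendees and their controls cannot be obtained, because 5 of its 14 days lie outside the window. The before/after comparison announced for that festival then cannot be carried out as described.

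The 9 and 21 days are exact. The ratios 1.56 and 2.33 are illustrations that rest on flat incidence, no festival effect and the use of raw counts without allowing for the length of the period. They describe change within a cohort and are not a bias in the attendee-versus-control result.

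A reader might go further and conclude that each control must be given the festival date of its paired attendee. The date error does not imply this: one fixed window per festival, shared by attendees and controls, resolves it. Counting by pair is a separate design question, and section 7.3 lists the control cohort's test results as aggregated, so it might need a different data transfer.

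**What to change.** Replace the single pair of dates in section 6.2 with two windows, each applied to the attendees and to their control cohort:

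- CanetRock: 19 June to 17 July 2021.
- Cruïlla: 24 June to 24 July 2021.

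Set the registry extraction dates to match. The cost is one sentence in the protocol and a changed date filter for the CanetRock extraction. If data have already been drawn on the printed dates, the CanetRock attendees and their controls need a supplementary extraction for 19 to 23 June, and 18 to 24 July should be left out of the 14-day count. The endpoint definition and the Cruïlla window stay as they are.

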### ***6.3 Treatment and exposure description***

For the Cruïlla Festival cohort, subjects with negative results at the SARS-Cov-2 Ag-RDT screening were exposed to the Cruïlla festival for 1, 2 or 3 days.

For the CanetRock Festival cohort, subjects with negative results at the SARS-Cov-2 Ag-RDT screening were exposed to the CanetRock festival for 1 day.

### ***6.4 Control group selection***

Prevalence of COVID-19 among those attending the Cruïlla festival or the CanetRock festival will be compared with the prevalence of COVID-19 in a control cohort. The control cohort will be created according to the characteristics of the attendees (gender, age, geographical area, and COVID-19 immune status).

### ***6.5 Sample size predetermination***

This is a retrospective cohort study, with no formal sample size calculation. Overall, 40000 people underwent SARS-CoV-2 antigen test within the Cruïlla festival and 22000 people underwent SARS-CoV-2 antigen test within the CanetRock festival. Those that are registered at the Catalan Health System will be paired with a control and included in the analysis.

## **7 VARIABLES AND MEASURE INSTRUMENTS. MEASUREMENTS DEFINITION AND DESCRIPTION**

### **7.1 Primary endpoint**

To study the prevalence of Covid-19 among those attending the festivals, the following endpoint will be analysed:

- Frequency of subjects attending to the Cruïlla festival who report a positive test on SARS-CoV-2 within the 14 days after the festival.
- Frequency of subjects attending to the CanetRock festival who report a positive test on SARS-CoV-2 within the 14 days after the festival.
- Frequency of subjects in each control cohort who report a positive test on SARS-CoV-2 within the 14 days after the festival.

Additional analysis will be performed excluding the following subjects, who will be considered as not infected during the festivals:

- Subjects who tested positive on SARS-CoV-2 6 days after their last day attending the festival.
- Subjects who tested positive within 2 days after attending the festival.

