### ***1.7 Design***

This is a retrospective cohort study comparing the incidence of Covid-19 between individuals that attended the Cruïlla music festival and a control cohort that did not attend this event. It will also compare the incidence of Covid-19 between individuals that attended the CanetRock music festival and its corresponding control cohort that did not attend this event.

The attendees and the control cohort will be paired according to the following characteristics: age, gender, geographical area and COVID-19 immune status (vaccine/reinfection). The study will compare the number of individuals who tested positive for Covid-19 in each cohort, before and after the festival.

Briefly, data identifying Cruïlla festival attendees and CanetRock festival attendees will be transferred to the Catalan Health Authorities, who will collect information regarding their Covid-19 vaccination status from the Public Health registries. Each attendee will be paired to a control subject (based on age, gender, geographical area and Covid-19 immune status). Then, the number of positive SARS-CoV-2 tests between attendees and

controls on the 14 days after the festival will be compared. Data regarding positive SARS-Cov-2 tests after the festival of the attendees and the control group will be collected from the Catalan Health Department registry.

This data will be transferred anonymously (without any personal identificatory) to investigators from the Germans Trias i Pujol Hospital and Lluita contra la Sida Foundation to be interpreted.

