### ***8.2 Statistical methods***

All variables will be described for the entire study sample and for each study group. To this end, the following analyses are foreseen:

- Continuous data will be described by their mean, median, standard deviation (SD), quartiles, minimum, and maximum.
- Categorical variables will be described by frequency and percentages (n, %).

Study endpoints will be analysed per groups and using frequencies, as described above in section 7.

No data imputation will be made. Only the subjects observed will be analysed and the number of missing data will be described in each analysis.

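### A before-and-after comparison with controls is announced, but section 7.1 defines only post-festival frequencies and no named analysis uses the pre-festival period

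*Protocol*

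**What the plan says.** The aim in Protocol section 3 (Rationale) is comparative and covers both periods: "This study aims to compare the prevalence of COVID-19 among those attending the Cruïlla festival and a control cohort, before and after attending the festival". The same section states this separately for CanetRock. Section 1.7 (Design) agrees: "The study will compare the number of individuals who tested positive for Covid-19 in each cohort, before and after the festival". Section 6.2 plans the data for it; positives "will be collected considering 14 days before and 14 days after the festival (24th June - 24th July").

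The endpoints do not follow. Section 7.1 lists three primary frequencies, all post-festival:

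- Cruïlla attendees: "Frequency of subjects attending to the Cruïlla festival who report a positive test on SARS-CoV-2 within the 14 days after the festival"
- CanetRock attendees: "Frequency of subjects attending to the CanetRock festival who report a positive test on SARS-CoV-2 within the 14 days after the festival"
- controls: "Frequency of subjects in each control cohort who report a positive test on SARS-CoV-2 within the 14 days after the festival"

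Section 7.2 profiles attendees by screening result and later positivity, with no control cohort and no pre-festival frequency. On endpoints, section 8.2 says: "Study endpoints will be analysed per groups and using frequencies, as described above in section 7". Section 1.7 itself moves to an after-only comparison in its operational paragraph, where positives in attendees and "controls on the 14 days after the festival will be compared".

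**The concern.** The protocol settles the central comparison in two incompatible ways: before and after in the aim, after only in the endpoints.

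This matters because section 3 expects the results to inform how well the festivals' preventive measures worked, which is a claim about cause. Controls are paired on age, gender, geographical area and immune status (sections 1.10 and 6.1). Social contact and testing habits are not paired, and both affect whether a person has a registry positive. If festival-goers differ from people who stayed away on either, the difference appears in the 14 days after the festival whether or not anyone was infected there. The pre-festival comparison is the planned element that could show this, and it has no endpoint.

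**Working it through.** **1. The sections side by side**

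| Protocol section | Period | Controls included? |
|---|---|---|
| 3 Rationale | before and after | yes |
| 1.7 Design, general statement | before and after | yes |
| 1.7 Design, operational paragraph | 14 days after | yes |
| 6.2 Observation period | 14 days before and 14 after | yes (each cohort) |
| 7.1 Primary endpoints | 14 days after | yes |
| 7.1 Additional analysis | excludes some post-festival positives by timing | not stated |
| 7.2 Secondary endpoints | screening result, then after | no |
| 1.6 and 4.1 Primary objective | no period given | no |

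The pre-festival period is in the aim, the design and the data collection. It is absent from every endpoint.

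**2. The window.** Section 3 dates CanetRock to 3 July and Cruïlla to 8–10 July 2021.

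- Cruïlla: 8 July − 14 days = 24 June; 10 July + 14 days = 24 July. This matches 6.2.
- CanetRock: 3 July − 14 days = 19 June; 3 July + 14 days = 17 July. The stated dates instead give 3 July − 24 June = 9 days before and 24 July − 3 July = 21 days after.

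**3. What an after-only ratio measures.** The protocol gives no rates, so this is an illustration under assumptions. Let *b* be the attendee/control ratio of registry positivity that would exist without the festival, and *f* the ratio due to the festival. On a multiplicative model:

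after-only ratio = *b* × *f*

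- With *f* = 1 and *b* assumed between 1.0 and 1.5, it reads 1.0 to 1.5.
- With *b* = 1.3 and *f* = 1.5, it reads 1.3 × 1.5 = 1.95.

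Large cohorts do not remove *b*. Assume 14-day control positivity of 0.5% to 2%, *f* = 1, and a two-sided 5% test of two unpaired proportions (the protocol names no test). The probability of declaring a difference is:

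| Assumed *b* | 40000 per group | 22000 per group |
|---|---|---|
| 1.10 | 0.16 to 0.51 | 0.11 to 0.31 |
| 1.25 | 0.66 to 0.998 | 0.42 to 0.94 |

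These use the full screened counts in section 6.5. The paired numbers will be smaller.

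**4. What the baseline can and cannot show.** An undistorted pre-festival ratio estimates *b*, and the ratio of ratios is (*b* × *f*) / *b* = *f*. Two features of the plan distort it.

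- *Selection.* Ticket holders who tested positive beforehand and returned their entrance are outside the screened cohort (section 7.3), and section 6.3 treats screen-negative subjects as the exposed. If this multiplies attendees' positivity just before the festival by *s* < 1, the ratio of ratios becomes (*b* × *f*) / (*b* × *s*) = *f*/*s*, which overstates *f*.
- *Pairing on previous infection.* No date is given for immune status. If it runs up to the festival, a positive in the baseline window counts as a previous infection, and pairing on it pushes the baseline ratio towards 1 whatever *b* is.

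**5. Precision.** With control positivity 1%, *b* = 1.25 and 40000 per group, the standard error of the log after-only ratio is √[(1 − 0.0125)/500 + (1 − 0.01)/400] = 0.067. If both periods have these rates and are treated as independent, the log ratio of ratios has standard error 0.067 × √2 = 0.094. At 22000 the figures are 0.090 and 0.127.

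**The case against.** - **A reader might infer that the pre-festival data will never be used.** The document does not support that. Section 8.2 opens by promising a description of every variable overall and by group, which could cover pre-festival positives. Its sentence on endpoints says how they are analysed and does not exclude other analyses. An unseen analysis plan could also add the comparison. What stands is that no endpoint or named contrast exists, and an analysis plan that made one primary would depart from 7.1.
- **The primary objective (1.6 and 4.1) is prevalence among attendees, with no before/after element.** This is correct. A reader might infer that a ratio of ratios should replace the primary contrast. That would be a redesign, and step 4 shows that it brings biases of its own.
- **The additional analysis in 7.1 already addresses attribution.** It does so in part, by setting aside positives whose timing is judged incompatible with infection at the festival. It does not remove background infections or extra testing in the days it keeps.
- **The illustrative ratios have no source in the protocol.** This is also correct. They show how a baseline difference carries through, not that one exists.
- **The extra work may be more than it seems.** Section 7.3 lists aggregated results for controls, while section 9.2 describes a merged pseudonymised database. If only aggregates arrive, a paired analysis of controls is unavailable and an unrequested window may not be recoverable. That is a reason to specify the window before extraction.

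**Conclusion.** The concern holds as a mismatch between the aim, design and data collection on one side and the endpoints on the other. As the endpoints stand, the contrast cannot show whether an excess among attendees pre-dates the festival.

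The size of any resulting bias is unknown. The figures 1.3, 1.25 and 1.95 rest on assumed baseline ratios, a multiplicative model and, for the probabilities, assumed positivity of 0.5% to 2%. A reader might go further and conclude that attendees do have a higher baseline, or that the study cannot answer its before/after question at all. Neither follows: the protocol gives no baseline rates, and 6.2 plans data for both periods in each cohort. The mismatch in the CanetRock window is plain calendar arithmetic and needs no assumption.

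This should be corrected, and doing so requires no new subjects.

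**What to change.** 1. In 7.1, add for each attendee cohort and each control cohort the frequency of subjects with a positive test in the pre-festival window.
2. Report the attendee-versus-control comparison for both periods. Give the before/after contrast, for example a ratio of ratios, as a supporting analysis; the post-festival frequencies remain primary.
3. Date the immune status used for pairing before the start of the baseline window, so that pairing on previous infection does not equalise the baseline.
4. State that screening and returned tickets lower attendees' positivity just before the festival. Add an earlier registry window as a sensitivity analysis, for example days −28 to −15. This lies outside 6.2, so 6.2 must be extended for it, and immune status must be dated before that window too when it is used.
5. Set the windows in 6.2 per festival: on its own 14-day rule, 24 June to 24 July for Cruïlla and 19 June to 17 July for CanetRock.
6. Say whether control results arrive as individual records or aggregates, and include the pre-festival windows in the data request.

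If an after-only comparison is intended, remove the pre-festival element from 1.7, 3 and 6.2 and temper the attribution of any difference to the festival.

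The cost is protocol wording and a little more extraction and analysis. The before/after contrast will have a wider interval, by a factor of about √2 on the log scale under the assumptions of step 5.
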